**3.6.2 Analysis Populations**

For the analysis of the primary and secondary outcomes, intention-to-treat (ITT) analysis was performed. The ITT population was defined as the population of all patients enrolled in this study. Because the ITT analysis included the data collected from patients who were lost to follow-up before treatment failure and because this fact might increase the likelihood of follow-up bias, a per-protocol (PP) analysis was carried out to detect the bias’ effect on the primary outcome. The PP population was defined as the population the in ITT analysis, excluding patients who were lost to follow-up before achieving the primary outcome.

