**2. STUDY OUTCOMES**

**2.1 Primary Outcome**

The primary outcome of this study is time to treatment failure

Treatment failure is defined as: in addition to other AEDs due to lack of efficacy; discontinuation of SRVPA or topiramate due to lack of efficacy, intolerable adverse events, lack of efficacy combined with intolerable adverse events, poor compliance, patients’ financial hardship, or a plan of pregnancy. A patient with poor compliance was defined as having discontinued SRVPA or topiramate treatment by his or her own volition.

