**3.5 Procedures**

The information recorded during the first visit included patient demographics, information about previous antiepileptic treatment, history of febrile seizures, birth traumas, epilepsy in first-degree family members, and neurological diseases (e.g., stroke, head injury, cortical development disorder, or intracerebral infection). A general physical examination and a neurological examination were performed. Laboratory examinations were carried out. Electrocardiogram (ECG) examinations were also performed, if necessary. Surface electroencephalography was performed on each patient to detect significant changes that might contribute to diagnosis. Computed tomography, magnetic resonance imaging and additional examinations, such as thyroid hormones, autoantibodies, and rheoencephalography, were carried out if clinically needed. Clinicians were asked to classify the types of epilepsy, epileptic syndromes, and types of seizures according to the criteria of the ILAE

The patients were asked to return for subsequent reviews at the second week, the first month, the third month, the sixth month and at successive half-year intervals from the date of initial medication. If clinical attention was necessary, more visits were scheduled between the regularly scheduled appointments. To control recall bias, each patient treated at our centres was asked to keep a medical diary with information on seizure onset, combinations with other drugs, adverse events, and hospital admissions. To control the loss of follow-up bias in the case of patients who did not appear for regular visits, follow-up data were obtained through telephone interviews or with structured questionnaire letters by mail. A patient who was lost of contact for more than one year was defined as a follow-up loss.

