**3.6 Statistical Analysis**

**3.6.1 Sample Size Calculation**

Sample size calculations were based on the primary outcome. It was assumed that the treatment failure for SRVPA and topiramate were 25% and 35% after one year, respectively. In this study, SRVPA was considered as an active comparator, there needed 415 patients for each group to achieve 90% power (β=0.1) at a 0.05 significance level to detect an equivalence hazard ratio of 1.35, assuming a dropout rate of 20% for both groups during the whole study.

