**3.6.3 Statistical Analysis Methods**

Kaplan-Meier estimates were used to describe the distribution of time to treatment failure, time to first seizure, time to 12-month remission, and time to 24-month remission. The log-rank tests were used to compare survival curves. The causes for censoring in Kaplan-Meier analysis were defined as follows: patients who were lost to follow-up, patients who died but whose death had no association with AED treatment and patients who were still receiving AED treatment at the end of this study. The censoring population was regarded as having no clinical outcome observed. Cox proportional hazard models (95% confidence interval) were used to analyse the relative risks expressed as hazard ratios (HR). In the final model, potential confounders (sex, age, type of epilepsy, seizure duration, number of previous AEDs and seizures at baseline) would be adjusted. Tolerability was assessed in the ITT population. To compare the reasons leading to treatment failure between SRVPA and topiramate, Chi-square tests and Fisher’s exact tests were used. The baseline characteristics of the two groups were compared using nonparametric tests, except the data represented as mean ± standard deviation (SD), which were analysed by using student’s t-test. All of the statistical analyses were performed with SPSS v. 13.0 software for Windows, using two-sided tests with a significance level of 0.05. No interim analysis is planned for this study.

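### The per-protocol check on loss to follow-up removes only patients without an observed failure, so its gap from ITT cannot separate attrition bias from unequal loss between the drugs

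*Protocol*

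**What the plan says.** Section 3.6.2 makes ITT the analysis for primary and secondary outcomes: "The ITT population was defined as the population of all patients enrolled in this study". It recognises that loss before failure may bias the result and says that "a per-protocol (PP) analysis was carried out to detect the bias" and its effect on the primary outcome. The PP set is ITT, "excluding patients who were lost to follow-up before achieving the primary outcome".

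Other sections bear on this:

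- Section 3.6.3 sets the censoring rule: "The causes for censoring in Kaplan-Meier analysis were defined as follows: patients who were lost to follow-up", with unrelated deaths and patients still on treatment at study end listed next.
- Section 3.5 defines loss: "A patient who was lost of contact for more than one year was defined as a follow-up loss". It also provides for telephone interviews and mailed questionnaires when visits are missed.
- Section 2.1 counts stopping through poor compliance as treatment failure: "A patient with poor compliance was defined as having discontinued SRVPA or topiramate treatment by his or her own volition".
- Section 3.6.1 assumes that "treatment failure for SRVPA and topiramate were 25% and 35% after one year", with 20% dropout in each group over the whole study.

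**The concern.** Whether a lost patient belongs to the PP set depends on the outcome. A patient who failed and then lost contact stays; one who lost contact without an observed failure is removed together with all the event-free time already accrued. Bias from loss depends on what happens to patients after contact ends, and the PP rule makes no assumption about that.

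The endpoint makes this matter. A patient who stops the drug unprompted and cannot be reached is a failure under section 2.1, yet is censored in ITT and deleted in PP, so neither analysis counts the event.

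At stake is how the comparison is read. This is the only analysis of the effect of loss that the protocol describes, in a study where drug choice was not randomised. Agreement between ITT and PP could reassure wrongly, and disagreement could be an artefact of unequal loss.

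**Working it through.** The protocol attaches no figure to the PP analysis, so there is none to reproduce. Inputs from section 3.6.1: one-year failure 25% (SRVPA) and 35% (topiramate), 20% dropout per group, 415 per group. Assumptions not in the documents: constant hazards, the loss rates by drug, and the follow-up lengths. The 7.5-year maximum used below follows from the visit schedule: Visit 1 at baseline, then 2 weeks and 1, 3 and 6 months (Visit 5), then half-yearly, so Visit 19 falls at 6 + 14 × 6 = 90 months. The one-year minimum is assumed.

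**Step 1. Direction.** The Kaplan-Meier estimate multiplies factors (1 − d/n) over failure times. Deleting a censored patient lowers n at every failure time up to that patient's last contact and leaves d unchanged. Each factor stays the same or falls, so PP failure is never below ITT failure.

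**Step 2. Size with the protocol's 20% loss, non-informative, one year of follow-up.** With failure hazard λ and loss hazard μ:

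- Lost before failure = μ/(λ+μ) × (1 − e^−(λ+μ)), set to 0.20.
- PP one-year failure = [λ/(λ+μ) × (1 − e^−(λ+μ))] / (1 − 0.20).
- SRVPA: λ = −ln 0.75 = 0.2877 and μ = 0.2597. Observed failures are 0.2877/0.5474 × 0.4216 = 0.2215, and 0.2215/0.80 = 27.7%.
- Topiramate: λ = −ln 0.65 = 0.4308 and μ = 0.2793. Observed failures are 0.4308/0.7101 × 0.5084 = 0.3084, and 0.3084/0.80 = 0.3855, about 38.6%.

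With 20% loss spread over 5 years, PP one-year failure is 30.0% and 41.5%. With an assumed 10% loss per year and follow-up of 1 to 7.5 years, it is about 30% and 40%. ITT Kaplan-Meier recovers 25% and 35%.

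**Step 3. Hazard ratio, topiramate against SRVPA.** Simulated large cohorts, unadjusted Cox model. Paired figures are SRVPA v topiramate.

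| Assumed scenario | True HR | ITT | PP |
|---|---|---|---|
| Non-informative loss, 10%/yr in both arms | 1.00 | 1.00 | 1.00 |
| Non-informative loss, 5% v 15%/yr | 1.00 | 1.00 | 1.18 |
| Non-informative loss, 15% v 5%/yr | 1.00 | 1.00 | 0.84 |
| Non-informative loss, 5% v 15%/yr | 1.50 | 1.50 | 1.69 |
| Non-informative loss, 15% v 5%/yr | 1.50 | 1.50 | 1.24 |
| 20% v 20% lost in 1 yr; hazard after loss ×5 on topiramate only | 1.32 | 1.00 | 1.00 |
| 10% v 30% lost in 1 yr; hazard after loss ×0.2 | 0.89 | 1.00 | 1.16 |
| 10% v 30% lost in 1 yr; hazard after loss ×1 | 1.00 | 1.00 | 1.16 |
| 10% v 30% lost in 1 yr; hazard after loss ×5 | 1.30 | 1.00 | 1.16 |
| 20% v 40% of failures hidden as losses, no other loss | 1.50 | 1.12 | 1.35 |
| The same hiding, no drug effect | 1.00 | 0.75 | 0.85 |

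Re-runs of the 5%/15% per year null case gave PP values of 1.17 to 1.19, and 0.84 to 0.85 reversed.

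**Step 4. Reading the table.** In the three 10% v 30% rows, PP stays at 1.16 while the truth runs from 0.89 to 1.30: the ITT-PP gap follows the loss imbalance, not the outcomes after loss. In the equal-loss row with bias there is no gap although the truth is 1.32. With hidden failures, PP recovers (1.35 − 1.12)/(1.50 − 1.12) = 0.23/0.38, about 60% of the error. It moves the right way because hiding more failures on topiramate also makes loss higher there.

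**Step 5. False positives at 415 per arm.** With no drug effect and non-informative loss, across follow-up of 1 to 5 years, a nominal 5% test on PP rejects in 9–24% of studies at 15% v 25% loss and 19–70% at 10% v 30%. ITT stays near 5%.

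**The case against.** The case for leaving the rule alone has several sound parts.

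- **A reader might infer that PP can never show attrition bias.** The figures do not support that. Where patients stop the drug and vanish more often on topiramate, PP departs from ITT and moves towards the truth. The fair statement is that the gap is ambiguous and the correction partial.
- **A reader might infer that PP always overstates failure.** It is never below ITT, but with 20%/40% of failures hidden and no other loss, PP one-year failure was 23%/30%, below the true 25%/35%. Overstatement relative to the truth is shown for non-informative loss.
- **The protocol assumes equal dropout.** With equal loss the null HR is undistorted, and a true HR of 1.52 gave 1.47 in PP at 10% loss per year in both arms. A 10-point difference in loss moves the null HR by only about 7–11%. The documents give no loss rate by drug, so every unequal split is an assumption.
- **Section 3.5 reduces the problem.** Telephone and mail contact will recover some patients who stopped unprompted. This limits loss; it does not analyse the effect of the loss that remains.
- **PP is supplementary.** It concerns the primary outcome only, and no decision rule depends on its agreement with ITT. The SAP is not at hand and may contain further analyses of loss.

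These points limit the size and reach of the concern. None changes the rule written in section 3.6.2, which selects on outcome.

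**Conclusion.** The point holds and should be fixed. The PP set selects on the outcome and is a poor check on loss to follow-up. Under non-informative loss it raises one-year failure from 25%/35% to about 28–30% and 39–41% with 20% lost per arm. Under the null it leaves the HR alone if loss is equal; it gives about 1.18 or 0.84 if loss is 5% and 15% per year in one direction or the other. A gap between ITT and PP cannot be attributed to bias rather than to unequal loss, and the absence of a gap does not exclude bias.

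These sizes rest on constant hazards and on loss patterns chosen for illustration; the direction in Step 1 needs neither. It would be wrong to conclude that the primary result is compromised: the ITT estimate, interval and test are untouched by the PP rule. Whether ITT itself is biased by loss is the question that this check leaves unanswered.

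**What to change.** In section 3.6.2:

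1. Keep ITT, with lost patients censored at last contact, as the main analysis.
2. Stop using the present PP set as the check on follow-up bias. Drop it, or keep it labelled as descriptive.
3. Add a sensitivity analysis that counts every lost patient as failed at last contact.
4. Add the two opposite extreme cases: lost topiramate patients failed and lost SRVPA patients event-free to study end, and the reverse.
5. Report whether the conclusion from the adjusted HR holds across these analyses.

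Inverse-probability-of-censoring weighting on baseline covariates is an optional addition. The cost is a change of wording in the protocol, matched in the SAP, and a few more model runs on data already held. No further data collection is needed.

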**3.6.3 Statistical Analysis Methods**

Kaplan-Meier estimates were used to describe the distribution of time to treatment failure, time to first seizure, time to 12-month remission, and time to 24-month remission. The log-rank tests were used to compare survival curves. The causes for censoring in Kaplan-Meier analysis were defined as follows: patients who were lost to follow-up, patients who died but whose death had no association with AED treatment and patients who were still receiving AED treatment at the end of this study. The censoring population was regarded as having no clinical outcome observed. Cox proportional hazard models (95% confidence interval) were used to analyse the relative risks expressed as hazard ratios (HR). In the final model, potential confounders (sex, age, type of epilepsy, seizure duration, number of previous AEDs and seizures at baseline) would be adjusted. Tolerability was assessed in the ITT population. To compare the reasons leading to treatment failure between SRVPA and topiramate, Chi-square tests and Fisher’s exact tests were used. The baseline characteristics of the two groups were compared using nonparametric tests, except the data represented as mean ± standard deviation (SD), which were analysed by using student’s t-test. All of the statistical analyses were performed with SPSS v. 13.0 software for Windows, using two-sided tests with a significance level of 0.05. No interim analysis is planned for this study.

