**3. METHODOLOGY**

**3.1 Study Design**

Observational cohort design is to assess the effectiveness of SRVPA and TPM in Chinese epileptic patients.

For the patients with a definite diagnosis of epilepsy, an appropriate AED was chosen by the clinicians, taking into consideration the efficacy and adverse events of the available AEDs, the clinical characteristics and the economic status of the patient. The patients also had the right to refuse the clinicians’ prescriptions and could discuss the drugs with the clinicians to decide which AED would be chosen.

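### Economic status influences drug choice and underlies one failure reason, but the adjustment list omits it and the deciding analysis is not named

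*Protocol*

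**What the plan says.** - **Design (protocol 3.1).** There is no randomisation: "Observational cohort design is to assess the effectiveness of SRVPA and TPM in Chinese epileptic patients". The clinician's choice of drug takes into account, among other things, "the clinical characteristics and the economic status of the patient". Patients could refuse a prescription and "could discuss the drugs with the clinicians to decide which AED would be chosen".
- **Primary outcome (2.1).** The reasons for discontinuation that count as treatment failure include "poor compliance, patients’ financial hardship, or a plan of pregnancy". Section 5 likewise allows removal at the patient's request for economic reasons.
- **Analysis (3.6.3).** "The log-rank tests were used to compare survival curves", with no stratification or weighting stated. Cox models give hazard ratios with 95% confidence intervals, and in the final model "potential confounders (sex, age, type of epilepsy, seizure duration, number of previous AEDs and seizures at baseline) would be adjusted". The section does not say which of the two analyses decides the primary comparison.
- **Baseline data (3.5).** The first-visit record covers demographics (not itemised), previous antiepileptic treatment and "history of febrile seizures, birth traumas, epilepsy in first-degree family members, and neurological diseases". No income, payment or insurance item is named.

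**The concern.** A variable that influences both which drug a patient receives and whether the patient reaches the endpoint is a confounder. The protocol gives economic status both roles: it is a stated ground for prescribing, and its direct consequence, stopping because of cost, is an endpoint event. The adjustment list is fixed at six variables and leaves it out. Because no economic item is named among the baseline data, a later analysis plan may be unable to repair this.

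A second gap adds to the first. With drug choice in the hands of clinician and patient, a log-rank test that adjusts for nothing compares two prescribing groups and does not isolate the drug effect. The adjusted Cox model comes closer. If the two disagree, the protocol does not say which one the conclusion follows.

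Bias in either direction matters. Section 3.6.1 describes 1.35 as an equivalence hazard ratio, so bias away from 1 can create a difference, and bias towards 1 can make unlike drugs look alike.

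**Working it through.** The protocol states no estimate of confounding bias, so there is no figure of its own to reproduce. It supplies only the scale: a hazard ratio (HR) of 1.35, one-year failure of 25% and 35%, and 415 patients per group (3.6.1). Whether 415 gives the stated power is a separate matter, and this point does not depend on it. **The strength of the economic effect, the prevalences and the hardship share below are all assumptions.**

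**1. Shift from one omitted binary factor.** Let g be the hazard ratio for failure with the factor, and p_T and p_S its prevalence in the topiramate and SRVPA groups. If the true HR is 1, the observed HR is about

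B = [1 + p_T(g − 1)] / [1 + p_S(g − 1)].

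| g | p_S / p_T | B |
|---|---|---|
| 1.25 | 40% / 60% | 1.15/1.10 = 1.045 |
| 1.5 | 40% / 60% | 1.30/1.20 = 1.083 |
| 2 | 40% / 60% | 1.60/1.40 = 1.143 |
| 2 | 30% / 70% | 1.70/1.30 = 1.308 |
| 2 | 20% / 70% | 1.70/1.20 = 1.417 |

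If the factor is instead more common on SRVPA, the shift is the reciprocal. The protocol does not say which group is the poorer.

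**2. Strength needed to reach 1.35.** Solving B = 1.35 gives g = 1 + 0.35/(p_T − 1.35 p_S):

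- 40%/60%: 1 + 0.35/0.06 = 6.8
- 30%/70%: 1 + 0.35/0.295 = 2.2
- 20%/70%: 1 + 0.35/0.43 = 1.8

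The largest shift from associations a (with drug) and b (with failure) is ab/(a + b − 1). Two-fold and two-fold give 4/3 = 1.333, just short of 1.35. The E-value for 1.35 is 1.35 + √(1.35 × 0.35) = 2.04. Under the conversion for common outcomes, 1.35 becomes a risk ratio of 1.231, and the E-value is 1.231 + √(1.231 × 0.231) = 1.76.

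**3. If economic status acts only through hardship stops.** Assume these make up 10% of the failure hazard in patients without the factor, and that the factor multiplies that component by 5. Then g = 1 + 0.10 × (5 − 1) = 1.4, and B is:

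- 40%/60%: 1.24/1.16 = 1.07
- 30%/70%: 1.28/1.12 = 1.14
- 20%/80%: 1.32/1.08 = 1.22

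**4. Effect on a two-sided 5% log-rank test.** The protocol's rates give 415 × 0.25 + 415 × 0.35 = 249 events at one year, before dropout. The mean of the test statistic is √(D/4) × ln(HR), where √(249/4) = 7.89.

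- True HR 1, B = 1.143: mean 7.89 × 0.134 = 1.05, so the test rejects 18% of the time.
- True HR 1, B = 1.308: mean 7.89 × 0.268 = 2.12, so it rejects 56% of the time.
- True HR 1.35 without bias: mean 7.89 × 0.300 = 2.37, power 66%.
- True HR 1.35 with a shift of 1.143 towards 1: 1.35/1.143 = 1.18, power 26%.

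More events do not help. With 467 events, the number that 90% power at HR 1.35 requires, the false rejection rate at B = 1.143 rises to 30%.

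**The case against.** The other side has five fair arguments.

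- **An adjusted analysis exists.** A reader might infer that the study rests on an unadjusted log-rank test alone. It does not: 3.6.3 specifies an adjusted Cox model, and 1.35 is on the hazard-ratio scale. Kaplan-Meier curves and a log-rank test followed by an adjusted Cox model are an ordinary sequence for a cohort, and an analysis plan that is not shown may name the deciding one.
- **The size is not shown.** A reader might infer that economic status alone could readily create or erase a hazard ratio of 1.35. The documents give no economic distribution, hardship share or direction of bias. Under moderate imbalance the shift is well short of 1.35.
- **Some handling is present.** Reasons for failure are compared between drugs by Chi-square and Fisher's exact tests, so an imbalance in hardship stops would be visible. Sex and age, which bear on planned pregnancy, are in the model. Demographics are not itemised, so it is not established that economic data go unrecorded.
- **Some hardship stops are a drug effect.** If one drug costs more, stopping because of cost is part of its real-world effectiveness. Adjusting for baseline economic status would not remove that part.
- **A long list of extra covariates is not warranted.** Collecting febrile-seizure history, family history or EEG does not make them confounders. The trend towards newer drugs in section 1 is general background and does not show drift during this study's enrolment.

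The first two limit how strongly the point can be put, and the last two limit the remedy. None removes the omission. A table of failure reasons cannot separate the patients' prior means from the cost of the drug. The protocol itself fixes the adjustment list, and no analysis plan can adjust for a variable that was not recorded.

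**Conclusion.** The point holds in a bounded form. The protocol names economic status as a ground for drug choice, counts stopping for financial hardship as failure, and leaves economic status out of its fixed adjustment list. It also leaves open whether the unadjusted log-rank test or the adjusted hazard ratio decides.

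The size and direction of the bias are unknown. Under the assumed strengths, moderate imbalance shifts the hazard ratio by about 1.05 to 1.14. Action through hardship stops alone gives 1.07 to 1.22 in the worked example. A shift of 1.35 needs associations slightly above two-fold with both drug and failure, or strong imbalance between the groups. The supported conclusion is that confounding could materially distort the comparison; that it would by itself produce or hide 1.35 is not supported. A shift of 1.14 is nevertheless enough to raise an 'unbiased' 5% error rate to about 18% at 249 events.

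**What to change.** - **Section 3.6.3:** name the covariate-adjusted Cox hazard ratio with 95% CI as the primary comparison, and label the Kaplan-Meier curves and log-rank test descriptive.
- **Sections 3.5 and 3.6.3:** record one economic item at the first visit, for example payment or insurance class, and add it to the adjustment list. If it cannot be obtained for patients already enrolled, report an E-value with the adjusted hazard ratio.
- **Section 3.6.3, for consideration:** add neurological-disease history, which is already collected, and use centre as a stratum.
- **Sensitivity analysis:** treat financial-hardship stops as a competing event and report the cause-specific hazard ratio for the other failure reasons. State that part of these stops may be a true effect of drug cost, so that the main and sensitivity results answer different questions.

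The cost is wording, one extra baseline field and a few more model parameters. If the economic item has three classes, it takes two parameters and neurological-disease history takes one. Against about 249 events at one year, that is a small price.

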**2.2 Secondary Outcomes**

Secondary clinical outcomes are the time to first seizure, the time from SRVAP or topiramate treatment to achieve 12-month remission of seizures, the time to 24-month remission of seizures. The incidence of clinically important adverse events and the incidence of intolerable adverse events directly leading to treatment failure were also analysed

Patients achieve 12-month (or 24-month) remission of seizures are defined as patients without any type of seizure for at least 12 months (or 24 months).

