**4.1 Adverse Events, Severity, and Relationship**

Adverse Event (AE): Any untoward medical occurrence in a subject or clinical investigation subject administered an investigational product. An AE does not necessarily have a causal relationship with the medicinal product. For this study the medicinal product is SRVPA or TPM.

All AEs encountered during the clinical study will be reported on the record. All AEs, regardless of relationship to study drug or procedure, should be collected beginning from the time the subject signs the study consent. AEs in clinical investigation subjects include any change in the subject’s condition. This includes symptoms, physical findings, or clinical syndromes.

An abnormal laboratory value may be considered an AE if the identified laboratory abnormality leads to any type of intervention whether prescribed in the protocol or not. It is up to the investigator to determine whether an abnormal laboratory value constitutes an AE. If an abnormal laboratory value is caused by a disease process, the disease process and not the laboratory abnormality should be listed as the AE (eg, if new onset viral hepatitis is causing elevated ALT, hepatitis and not the elevated ALT should be listed as the AE).

Examples of laboratory abnormalities which should be considered as AEs include those which result in withdrawal of the study treatment, withholding study treatment pending some investigational outcome, reduction of dose of the study treatment, or additional concomitant treatment. All laboratory abnormalities considered to constitute an AE should be reported on the appropriate AE page of the record.

Laboratory abnormalities do not need to be listed as separate AEs if they are considered to be part of a clinical syndrome that is being reported as an AE. It is the responsibility of the investigator to review all laboratory findings in all subjects.

Abnormal values should be commented upon as to clinical relevance or importance on the record or the laboratory report as appropriate. Medical and scientific judgment should be exercised in deciding whether an isolated laboratory abnormality should be classified as an AE.

**Every effort must be made by the investigator to categorize each AE according to its severity and its relationship to the study treatment.**

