**4.4 Intolerable Adverse Events**

Intolerable adverse event include any adverse event leading to treatment failure, such as: event results in death, event is life-threatening (Note: The term “life-threatening” refers to an event in which the subject was at risk of death at the time of the event; it does not refer to an event which hypothetically might have caused death if it were more severe.), event requires inpatient hospitalization or prolongation of existing hospitalization, event results in persistent or significant disability/incapacity, event is a congenital anomaly/birth defect and event leading to SRVPA or TPM withdraw.

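### Clinically important adverse events are analysed by starting drug with no stated end to counting, so events after an add-on or switch can be charged to the starting drug and dilute the comparison

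*Protocol*

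**What the plan says.** Section 2.2 names two safety outcomes: "The incidence of clinically important adverse events and the incidence of intolerable adverse events directly leading to treatment failure were also analysed". Section 3.6.2 places all primary and secondary outcomes under ITT analysis: "The ITT population was defined as the population of all patients enrolled in this study". Section 3.6.3 repeats the choice for safety: "Tolerability was assessed in the ITT population". The only other population, per-protocol, is reserved for the primary outcome.

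On collection, section 4.1 says: "All AEs, regardless of relationship to study drug or procedure, should be collected beginning from the time the subject signs the study consent". It gives no end date and no rule for a change of drug. It also says "For this study the medicinal product is SRVPA or TPM", without separating the starting drug from the other one.

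On what happens after failure:
- Section 2.1 counts the addition of another antiepileptic drug for lack of efficacy as treatment failure, alongside discontinuation of the starting drug for several reasons.
- Section 3.5 schedules half-yearly visits counted from the start of medication, and does not say that they stop at failure.
- The section 3.3 schedule has adverse events recorded at every visit from Visit 1 to Visit 19.
- Section 5 lists the reasons for removal: a serious or intolerable event, intercurrent illness, or patient request. Neither add-on nor lack of efficacy is on the list.

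**The concern.** Analysis by starting drug over all follow-up suits time to treatment failure, because the clock stops when the starting drug fails. It suits drug tolerability less well. A patient who adds a second drug and stays under observation goes on contributing events to the group of the first drug, although those events may come from the second drug or from the combination. The same holds for a patient who switches and is still followed.

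The causality rating does not fully separate these events. After a switch from one study drug to the other, an event caused by the second drug is still related to SRVPA or topiramate in the sense of sections 4.1 and 4.3. Collection is in any case regardless of relationship.

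The protocol itself expects the two drugs to fail at different rates, so the share of follow-up spent after failure would differ between groups. At stake is the readability of one secondary outcome, the incidence of clinically important adverse events.

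**Working it through.** The protocol gives no adverse-event rate and no figure for time after failure, so there is no figure of its own to reproduce on this point.

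**Step 1: how long post-failure observation could last.** Take Visit 1 as baseline (section 4) and the section 3.5 intervals. Visits 2 to 5 fall at 2 weeks, 1, 3 and 6 months, and each later visit adds 6 months. Visit 19 is then at 6 + 14 × 6 = 90 months, or 7.5 years. Horizons of 2 and 5 years are within the schedule.

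**Step 2: share of follow-up after failure.** Inputs: one-year failure of 25% and 35% (section 3.6.1). Assumptions: constant hazards, and follow-up that continues after failure.
- Hazards: h = −ln(0.75) = 0.288 per year (SRVPA); h = −ln(0.65) = 0.431 per year (topiramate).
- Mean time before failure over horizon T: (1 − exp(−hT))/h. Post-failure share: 1 − that/T.

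| T | SRVPA before failure | Post-failure | Topiramate before failure | Post-failure |
|---|---|---|---|---|
| 2 years | 1.52 years | 24% | 1.34 years | 33% |
| 5 years | 2.65 years | 47% | 2.05 years | 59% |

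No assumed adverse-event rate enters these shares.

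**Step 3: effect on the comparison (illustration).** Assume a first clinically important event at rate a = 0.05 per year on SRVPA and 0.15 on topiramate, and rate b after failure. The incidence by starting drug is 1 − [exp(−(h + a)T) + ∫₀ᵀ h·exp(−ht − at − b(T − t)) dt].

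| Later treatment, T = 5 years | SRVPA | Topiramate |
|---|---|---|
| No failures (reference) | 22.1% | 52.8% |
| Every failure is an add-on, b = 0.05 + 0.15 = 0.20 | 43% | 59% |
| 20% cross over, the rest take a drug with b = 0.10 | 31.9% | 43.2% |
| Every failure crosses to the other study drug | 37.4% | 35.8% |

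The risk ratio falls from 52.8/22.1 = 2.4 to 59/43 = 1.4 with add-ons alone. Full cross-over removes the difference at 5 years, but at shorter horizons it does not: 6.1% v 12.3% at 1 year, 13.6% v 20.7% at 2 years, 21.6% v 26.8% at 3 years.

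**Step 4: can the gap widen?** Assume on-drug risks of 10% v 20%, failure in 25% v 35%, and a 30% later risk in both groups. The incidences are 1 − 0.90 × (1 − 0.25 × 0.30) = 16.75% and 1 − 0.80 × (1 − 0.35 × 0.30) = 28.4%. The gap grows from 10.0 to 11.65 points, so the direction depends on what failing patients take next, which the protocol does not state.

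**Step 5: does a crude on-treatment percentage solve it?** Stopping the count at failure gives a/(a + h) × (1 − exp(−(a + h)T)). At 5 years, with the step 3 rates, this is 12.1% v 24.4%, a ratio of 2.0 against a true rate ratio of 0.15/0.05 = 3. Topiramate patients are observed for less time because they fail sooner. A rate per patient-year recovers the threefold ratio; a crude percentage does not.

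**The case against.** The strongest reply is that section 3.6.3 fixes a population, not a counting period. No sentence says that post-failure events belong to the starting drug, and no test is named for the incidence of clinically important events; the chi-square and Fisher tests there concern reasons for failure. Counting windows are often set in the SAP, which is not at hand. This stands to the extent that misattribution is a consequence the text permits, not one it orders. It does not remove the point: the protocol states twice that this outcome is analysed by ITT, and names no other safety analysis.

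Section 5 can also be read as ending data collection at removal, and its reasons overlap with some failure reasons. That may shorten post-failure follow-up after adverse events or patient requests. It does not cover add-on for lack of efficacy.

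For a third drug, section 4.2 asks the investigator to weigh factors unrelated to study treatment, and drug combinations are recorded. This helps interpret single events, but does not define the incidence count.

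An all-follow-up count by starting strategy is also a legitimate quantity in an effectiveness cohort. That stands, and is a reason to keep it as a sensitivity analysis.

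Three stronger readings are tempting, and the documents do not support them:
- **The whole safety comparison is compromised.** It is not. Section 4.4 ties the other outcome to failure of the starting drug: "Intolerable adverse event include any adverse event leading to treatment failure".
- **A true difference would vanish or reverse.** That needs assumed event rates with near-universal cross-over and long complete follow-up, or a small true gap, or very unequal later risks. The protocol says nothing about cross-over on that scale.
- **Events before the first dose distort the count.** Section 4.1 starts collection at consent, but the section 3.3 schedule begins recording at Visit 1, where prescribing also begins, and section 3.2 enrols patients treated with one of the two drugs. Restricting to patients with at least one dose would change almost nothing.

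**Conclusion.** The point holds for clinically important adverse events only. As written, the analysis allows events after an add-on, or after a switch in patients still followed, to count against the starting drug. If follow-up continues after failure and hazards are constant at the protocol's own failure rates, about 24% v 33% of follow-up at 2 years and 47% v 59% at 5 years falls in that period. If follow-up ends at some failures, the shares are smaller, with add-on failures as the group most clearly affected.

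The likely consequence is dilution. Its size depends on event rates and later treatments that the protocol does not give, so the step 3 percentages are illustrations, not estimates. The change should be made; the primary outcome does not depend on it.

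**What to change.** In section 3.6.3, specify for clinically important adverse events:
- **Main comparison:** the event rate per patient-year on the starting drug, or time to first event censored at the end of the window.
- **Window:** from first dose to the earlier of (a) the last dose of the starting drug plus a prespecified lag, or (b) the date another antiepileptic drug is added.
- **Later events:** listed separately by the treatment then being taken.
- **Sensitivity analysis:** the all-follow-up ITT incidence by starting drug.

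A crude on-treatment percentage should not be the main summary, because unequal failure cuts observation short by different amounts (step 5). The outcome of intolerable events leading to failure needs no change.

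The cost is wording and one derived variable. The last-dose date is recorded at removal (section 5), and drug combinations are recorded in diaries (section 3.5) and judged at most visits (section 3.3). The downside is that some late effects of the starting drug move to the separate listing; the lag limits this.
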